#### Safety and secondary analyses

Secondary and safety parameters will be summarized using descriptive statistics, i.e. number (%) of patients for categorical variables and mean, SD (standard deviation), median, minimum/maximum for continuous variables. Descriptive statistics will be produced by the treatment group. No formal hypothesis testing will be performed. Appropriate statistical tests will be applied in an explorative manner only. Occurrence of adverse events (safety) will be compared between treatment groups using chi-square tests and Fisher`s exact tests, as appropriate. Analyses of secondary endpoints will be analysed with appropriate statistical tests such as ANOVA for repeated measurements, paired and unpaired *t*-tests as well as their non-parametric equivalents.

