### Outcomes {12}

Primary endpoints:Efficacy: Improvement in LVEF measured by cardiac MRI from baseline to 360 days.Safety: Occurrence of device-related complications (adverse device effects or serious adverse device effects) within 360 days.

Secondary endpoints:Endpoints related to the efficacy are changes in the following parameters within a time frame of 360 days:6-min walk test distanceNYHA functional classSerum nt-proBNP levelsRenal function, measured by glomerular filtration rate (GFR)Seattle Angina Pectoris Questionnaire (SAQ)36-item short-form survey (SF36)Minnesota Living with Heart Failure Questionnaire (MLHFQ)Secondary safety-related endpoints include the following observations within a time frame of 6 days:Occurrence of ventricular arrhythmia during the hospital stayOccurrence of device-related peri-operative myocardial damage detected by a rise of cardiac biomarkers: creatine kinase (CK-MB) and troponin T (TropT)Occurrence of signs of device-related infection detected by a rise of C-reactive protein (CRP) or leukocytosis during the hospital stay

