### Interim analyses {21b}

Two main analyses are planned: (a) An interim analysis when at least 20 participants per group had finished their 360-day follow-up for the primary endpoints, to assess the safety and to allow for an early halt to the recruiting process. (b) A final analysis after 80 patients. For both analyses, the significance level alpha will be set to 0.0294 according to the alpha spending plan proposed by Pocock.

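### The protocol conflicts on whether the primary safety endpoint is tested at 0.0294, and the counts and difference test it gives cannot support a safety conclusion at 20 or 40 per arm

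*Protocol article*

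**What the plan says.** Objectives {7} lists the device's safety profile first among the primary objectives. Outcomes {12} makes the primary safety endpoint "Occurrence of device-related complications (adverse device effects or serious adverse device effects) within 360 days".

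The section Safety and secondary analyses, under {20a}, then puts safety with the secondary parameters:
- Descriptive output: "Secondary and safety parameters will be summarized using descriptive statistics, i.e. number (%) of patients for categorical variables", by treatment group.
- Status of tests: "No formal hypothesis testing will be performed. Appropriate statistical tests will be applied in an explorative manner only".
- Comparison between arms: "Occurrence of adverse events (safety) will be compared between treatment groups using chi-square tests and Fisher`s exact tests, as appropriate".

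Interim analyses {21b} plans "An interim analysis when at least 20 participants per group had finished their 360-day follow-up for the primary endpoints, to assess the safety". Its other stated purpose is that recruitment may stop early; the final analysis comes at 80 patients. It adds: "For both analyses, the significance level alpha will be set to 0.0294 according to the alpha spending plan proposed by Pocock".

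The Data Safety Monitoring Board section {21a} sends all captured adverse events to the board and gives no numerical rule. The Efficacy analysis section gives LVEF, the other primary endpoint, a mean with 95% confidence intervals.

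**The concern.** There are two linked problems.

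First, the status of safety is unclear. Outcomes and Interim analyses treat it as a primary endpoint examined at two looks with a stated alpha. Safety and secondary analyses removes it from formal testing. Two analysts could follow the text and differ on whether a safety p-value of 0.04 crosses the planned threshold.

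Second, the only inferential tool named is a test of no difference, in a trial sized on LVEF alone. A non-significant result at 20 or 40 per arm is compatible with a substantial excess of complications. A primary safety objective needs a statement of how large an excess the data exclude, and the stated output does not produce one. A Pocock level guards against a false claim of benefit. Applied to harm, it makes a signal harder to declare.

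**Working it through.** **The plan's own figures.** Sample size {14}, conservative method: d = (10.4 − 4.5)/8.7 = 0.678. A two-sample t-test at two-sided 0.05 and 80% power needs 36 per arm, 72 in total, and 72/0.90 = 80. Two equally spaced looks at 0.0294 give an overall two-sided alpha of 0.0500. Both figures reproduce. Neither involves safety.

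**Inputs for safety.** From the protocol: 20 per arm at interim, 40 per arm at the end, and alpha 0.0294 if it applies. Assumed: two-sided tests and all event rates, because the protocol states neither.

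**Miss probability.** Let X be the events in the sham arm and Y those in the device arm, independent binomials.

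P(miss) = 1 − Σ P(X = x)·P(Y = y), summed over tables with y > x and p ≤ 0.0294.

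When the sham rate is 0, this reduces to a binomial tail. With no sham events, Fisher needs 6 device-arm events at either sample size and uncorrected chi-square needs 5. Fisher's p for y vs 0 is 2·C(n,y)/C(2n,y):
- 6/20: 2 × 38,760/3,838,380 = 0.020
- 6/40: 2 × 3,838,380/300,500,200 = 0.026
- 5/40: 2 × 658,008/24,040,016 = 0.055

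For 0% vs 20% at 40 per arm, the miss probability is therefore P(Bin(40, 0.2) ≤ 5) = 16.1% with Fisher and P(Bin(40, 0.2) ≤ 4) = 7.6% with chi-square.

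| Assumed rates, sham vs device | Interim, 20/arm (chi-square to Fisher) | Final, 40/arm (chi-square to Fisher) |
|---|---|---|
| 0% vs 10% | 96–99% | 63–79% |
| 5% vs 20% | 83–92% | 54–65% |
| 5% vs 30% | 53–70% | 17–24% |
| 0% vs 20% | 63–80% | 8–16% |

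For 5% vs 20%:
- With the planned 36 evaluable per arm, the final figure is 59–70%.
- If 0.05 applied instead, the figures would be 71–83% at interim and 43–59% at the end.
- About 88 per arm (101 with continuity correction) would be needed for 80% power at 0.0294.

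**What an interval would show.** The exact two-sided 95% upper bound for 0 events in n is 1 − 0.025^(1/n), which is 16.8% for n = 20 and 8.8% for n = 40.

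Take 5/40 vs 0/40, where Fisher gives p = 0.055. The Wilson limits are 5.5% to 26.1% for 5/40 and 0% to 8.8% for 0/40. The Newcombe 95% interval for the difference is:
- lower: 12.5 − √[(12.5 − 5.5)² + 8.8²] ≈ 1.3 points
- upper: 12.5 + (26.1 − 12.5) = 26.1 points

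Uncorrected chi-square on the same table is 80 × (5 × 40)²/(40 × 40 × 5 × 75) = 5.33, p ≈ 0.021. The verdict at 0.0294 would therefore turn on which of the two named tests is used. The interval shows the plausible excess in either case.

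**The case against.** The best defence is that safety is meant to be descriptive. Counts by arm come first, the tests are labelled exploratory, and the board reviews all adverse events without a p-value threshold. The main hypotheses are written for LVEF only, so 0.0294 most naturally belongs there, and the mention of primary endpoints in {21b} may only describe completed follow-up. The test is stated for adverse events, a broader category than device-related complications. Interval methods are often left to a statistical analysis plan, and low power for safety is common in a trial of 80.

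Much of this stands. A reader might infer that safety is read out only through p-values, or that a non-significant result will be declared safe. The documents support neither: they give counts and board review, and nowhere equate non-significance with safety. A reader might also infer that real harm would usually be missed. At the final analysis that depends on the assumed rates and fails for 0% vs 20% and 5% vs 30%. A sham rate near 0% is plausible with an inactive applicator. The missing interval would not, on its own, be a finding in a condensed article.

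What does not fall is the conflict. Interim analyses names safety as a purpose and then sets one alpha for both analyses without confining it to LVEF. The article also goes beyond silence: it names a comparison for safety, and that comparison cannot answer the primary objective.

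**Conclusion.** The point holds in two parts. The protocol is inconsistent on whether its primary safety endpoint is formally tested at 0.0294; this follows from the text and needs no assumption. The difference test it names cannot support a safety conclusion at the planned size. That a large excess could go undetected rests on assumed event rates and two-sided testing. At interim, every scenario tried is missed more often than not (53–99%). At the final analysis the range is wide, from 8–16% to 63–79%. That 0.0294 governs safety is one reading of an ambiguous passage, not a stated rule. The wording should be corrected, but the defect does not touch the LVEF analysis.

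**What to change.** In Interim analyses {21b}, state that 0.0294 applies to the LVEF test only.

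In Safety and secondary analyses:
- Name the primary safety endpoint explicitly. Report it as number (%) per arm with exact (Clopper-Pearson) 95% intervals, and give the risk difference with a 95% interval, for example Newcombe.
- Keep any chi-square or Fisher p-value as exploratory.
- State that a non-significant difference is not evidence of safety.

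Give the interim safety review by the monitoring board the same estimates and bounds.

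The cost is wording and an extra table column, with no new data or patients. The downside is a less favourable safety statement, because the intervals will be wide. Trial status reports recruitment closed on 01.06.2022, so halting recruitment early is no longer at issue; the reporting change still applies to the final analysis.

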## Statistical methods

### Statistical methods for primary and secondary outcomes {20a}

#### Efficacy analysis

The primary efficacy variable is the LVEF absolute change from baseline, i.e. the intra-patient difference or change between the pre-treatment (baseline) value day 0 and the value measured at day 360. This variable is quantitative and continuous and will be presented as a mean value with 95% confidence intervals. Change in mean (μ) LVEF from baseline to day 180, defined as delta ΔLVEF, will be analysed using an analysis of covariance (ANCOVA) adjusted for LVEF at baseline (as outlined in Guideline on adjustment for baseline covariates in clinical trials EMA/CHMP/295050/2013, 5.6 ‘change from baseline’ analyses) The main study hypotheses will thus be formulated as:

$$\begin{array}{c}\mathrm H0:\;\mathrm\mu\;\;\mathrm{{\triangle}LVEFcontrol}\;=\;\mathrm\mu\;\;\mathrm{{\triangle}LVEFshockwave}\\\mathrm H1:\;\mathrm\mu\;\;\mathrm{{\triangle}LVEFcontrol}\;\neq\;\mathrm\mu\;\;\mathrm{{\triangle}LVEFshockwave}\end{array}$$

In case of severe deviations from a normal distribution, the change in LVEF from baseline to day 360 will be analysed with the non-parametric Mann-Whitney U test.

Additionally, ANOVA for repeated measurements will be applied in order to analyse LVEF changes across the full study period (day 0, day 180, day360).

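### The tests named for the exploratory secondary endpoints include no baseline-adjusted between-arm comparison, and one of them, the paired test, does not compare the arms

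*Protocol article*

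**What the plan says.** Outcomes {12} in the protocol article defines the secondary efficacy endpoints as "changes in the following parameters within a time frame of 360 days" and lists 6-minute walk distance, NYHA class, NT-proBNP, GFR, SAQ, SF-36 and MLHFQ. A change cannot be formed without a baseline value.

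Safety and secondary analyses first sets the status of these analyses: "Descriptive statistics will be produced by the treatment group", "No formal hypothesis testing will be performed", and "Appropriate statistical tests will be applied in an explorative manner only". It then gives examples of tests for the secondary endpoints, "such as ANOVA for repeated measurements, paired and unpaired" *t*-tests, together with their non-parametric equivalents. No baseline-adjusted model appears among them.

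Under Efficacy analysis, the LVEF change "will be analysed using an analysis of covariance (ANCOVA) adjusted for LVEF at baseline", and a regulatory guideline on baseline covariates is cited in support.

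**The concern.** The article adopts baseline adjustment for the primary endpoint and gives a reference for it. It then names only unadjusted methods for other continuous endpoints of the same form, without giving a reason. Two consequences follow.

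- **Precision.** With about 36 evaluable patients per arm, secondary estimates will have wide intervals. Leaving out a covariate that has already been measured makes them wider than they need to be.
- **The question answered.** The trial is a sham-controlled superiority comparison. A paired test looks at change within one arm. Both arms undergo CABG, and medical therapy may still be optimised between surgery and the follow-up visits. Within-arm improvement can therefore arise with no contribution from shockwave.

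What is at stake is how the walk-distance, symptom and quality-of-life results are read. No confirmatory claim is involved.

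**Working it through.** **Inputs.** The conservative method under Sample size {14} gives a mean LVEF improvement of 10.4 (SD 8.7) with intervention and 4.5 (SD 8.7) with control, 36 analysed per arm, two-sided alpha 0.05, power 0.80 and 10% loss. The liberal method gives a control SD of 5.76. The protocol gives no mean, SD or correlation for any secondary endpoint. LVEF is therefore only a stand-in, and the baseline/follow-up correlation r is assumed over 0.3 to 0.8.

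**Reproducing the plan's figure.** d = (10.4 − 4.5)/8.7 = 5.9/8.7 = 0.678. A two-sample *t*-test then needs 36 per arm (power 0.81). A Mann-Whitney test with relative efficiency 3/π needs 37. Enrolment is 72/0.90 = 80. The stated size reproduces, and this point does not alter it.

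**Precision of the between-arm comparison.** Assume the same SD σ at baseline and follow-up.

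- Variance of a change score: 2σ²(1 − r)
- Residual variance under ANCOVA: σ²(1 − r²)
- Ratio, ANCOVA to change score: (1 − r²)/[2(1 − r)] = (1 + r)/2

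| assumed r | variance ratio | reduction in standard error, 1 − √ratio |
|---|---|---|
| 0.3 | 0.65 | 19% |
| 0.5 | 0.75 | 13% |
| 0.7 | 0.85 | 8% |
| 0.8 | 0.90 | 5% |

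These ratios are large-sample values. With only two time points, the group-by-time test in a repeated-measures ANOVA equals the *t*-test on change, so the same ratios apply to it.

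To illustrate the scale, take 36 per arm and a change-score effect of d = 0.678. Power is 0.81 with a *t*-test on change. With ANCOVA the effective d is 0.678/√[(1 + r)/2], and power is 0.94 (r = 0.3), 0.91 (r = 0.5) or 0.85 (r = 0.8).

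**The within-arm test.** Take the plan's own control-arm assumption, in patients who receive no shockwave. If the observed values equal the assumed ones, t = 4.5/(8.7/√36) = 4.5/1.45 = 3.10 on 35 degrees of freedom, p = 0.004. Over repeated trials, a paired test in that arm would be significant at two-sided 0.05 with probability 0.855 (SD 8.7) or 0.995 (SD 5.76). A significant within-arm change is thus what the plan expects of the sham arm on LVEF. The same logic carries over to any secondary endpoint that CABG improves, although its size there cannot be computed from the protocol.

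**The case against.** The strongest reply is that the section answers the concern itself. It rules out formal hypothesis testing and calls the tests exploratory. It introduces the list as examples, so baseline adjustment is not excluded, and an analysis plan that is not shown may specify it. All of that stands, and it is why the point is minor. It does not remove the point. The article does name methods, one of them does not compare the arms, and an exploratory estimate should still be an estimate of the device effect.

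It is also fair that an unpaired test on change and the group-by-time term both compare the arms and both use baseline. They are valid. The only charge against them is the loss of precision shown above, which is modest at the higher correlations.

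A reader might infer more than the protocol supports:

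- *That NT-proBNP will be analysed untransformed despite skewness.* No scale is stated, and non-parametric equivalents are allowed.
- *That repeated-measures ANOVA will drop every patient with a missed visit.* The intention-to-treat section applies last observation carried forward where appropriate, so such loss is not established. Whether that method is sound is a separate question.
- *That much larger precision losses apply, as they would against a test of follow-up values alone.* The endpoints are defined as changes, so the change score is the relevant comparator.
- *That the plan licenses a claim of efficacy from improvement within the shockwave arm.* Nothing in it gives a paired test that standing.

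**Conclusion.** The point holds as a minor improvement. The named methods omit the more precise between-arm analysis that the same article uses for its primary endpoint. The gain is about 5% to 19% in standard error against a change-score test, for an assumed r of 0.8 to 0.3, equal SDs at the two times and large-sample formulas. The actual gain for each endpoint is unknown, because the protocol gives no correlations or SDs for them. Separately, and whatever r is, a paired within-arm test cannot separate shockwave from the CABG given to both arms. The LVEF arithmetic illustrates that confounding and does not measure it for any secondary endpoint. The sample size and the primary conclusion are unaffected.

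**What to change.** State that each continuous secondary endpoint is compared between arms at day 360 by ANCOVA with its own baseline value as covariate, and reported as an adjusted difference with a 95% confidence interval. Keep the exploratory status. Add that any paired within-arm test is descriptive and is not evidence of a shockwave effect.

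This costs a few sentences in the analysis plan, written before the treatment code is opened to the analysts. It needs no new data, visits or patients.

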### Interim analyses {21b}

Two main analyses are planned: (a) An interim analysis when at least 20 participants per group had finished their 360-day follow-up for the primary endpoints, to assess the safety and to allow for an early halt to the recruiting process. (b) A final analysis after 80 patients. For both analyses, the significance level alpha will be set to 0.0294 according to the alpha spending plan proposed by Pocock.

### Methods for additional analyses (e.g. subgroup analyses) {20b}

No subgroup analyses have been planned for this trial. To investigate the robustness of the primary endpoint analysis performed in the intention-to-treat (ITT) population and to examine the possible effects of missing data, sensitivity analyses are planned. These analyses will be performed in the ITT population without the imputation of missing values, in a population with complete data sets only, and in an ITT population where the LVEF of deceased patients is set to 0%.

### Methods in analysis to handle protocol non-adherence and any statistical methods to handle missing data {20c}

The following populations will be used for statistical analysis:

#### Intention-to-treat population

The intention-to-treat population will consist of all patients who were enrolled to the study and who have given their informed consent. In case of withdrawals and missing data, the Last observation carried forward (LOCF) procedure will be applied where appropriate. The ITT population serves as the primary analysis population.

#### Modified intention-to-treat population

The modified intention-to-treat population will consist of all patients who were enrolled to the study and were clinically evaluable (per cardiac MRI).

#### Per-protocol population

The per-protocol population will include all patients who received shockwave or control treatment without major protocol deviations. Major protocol deviations will be determined and documented prior to database lock.

### Plans to give access to the full protocol, participant level-data and statistical code {31c}

The full protocol of the study will be published together with a manuscript on the results of the clinical trial. The datasets analysed during the current study and the statistical code will be available from the corresponding author on reasonable request.

## Oversight and monitoring

### Composition of the coordinating centre and trial steering committee {5d}

As this is a single-centre trial the responsibilities of a steering committee will be covered by the principal investigator and the team of co-investigators. The Steering Committee will concentrate on the progress of the study, adherence to the protocol, patient safety and consideration of new information relevant to the research question. The trial quality will be independently monitored by the Competence Centre for Clinical Trials at the Medical University of Innsbruck. The study monitor will check 100% of trial data files at least once every 6 months.

### Composition of the data monitoring committee, its role and reporting structure {21a}

#### Data Safety Monitoring Board (DSMB)

An independent committee is established by the sponsor to assess at intervals, the progress of the clinical investigation, the safety data or the critical performance endpoints and to recommend the sponsor whether to continue, suspend, modify, or stop the clinical investigation.

The DSMB will be responsible for independently evaluating the safety of the patients participating in the trial. All captured adverse events and safety reports will be reported to the DSMB for assessment. All SAEs will be forwarded to the DSMB immediately after knowledge of it. The DSMB can, if required, amend the protocol and in case the risk to the patients outweighs the potential benefit, end the study prematurely. The members of the DSBM will consist of a cardiac surgeon and a cardiologist.

#### Adverse event reporting and harms {22}

An adverse event is the appearance or worsening of any undesirable sign, symptom, or medical condition occurring during or after the treatment (DESWT + CABG). Medical conditions/ diseases present before the treatment will only be considered adverse events if they worsen after the treatment. Abnormal laboratory values or test results constitute adverse events only if they induce clinical signs or symptoms, are considered clinically significant, or require therapy. The occurrence of adverse events should be sought (1) direct contact to the treating physicians, (2) screening of medical records and laboratory data for anticipated adverse events listed in the CRF and (3) by non-directive questioning of the patient at each visit during the study. Adverse events also may be detected when they are volunteered by the patient during or between visits or through physical examination, laboratory test, or other assessments.

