#### Experimental (intervention) arm

In the intervention arm, 300 shockwave impulses per coronary supply territory, at an energy flux density of 0.38mJ/mm2 and a frequency 3Hz, are applied in direct contact with the ischaemic myocardium of the left ventricle. The intervention is performed during CABG surgery after bypasses are fully established while still on cardiopulmonary bypass by the same cardiac surgeon performing the CABG procedure whom the principal investigator delegates. No specific surgical skills are needed for the application of DESWT with the Cardiac Shockwave Probe; however, investigators performing the procedure are trained and supervised by both the principal investigator and technicians to ensure reproducibility.

The cardiac shockwave system consists of a table-top device (Nonvasiv Medical GmbH, Konstanz, Germany) and a sterile single-use applicator releasing electrohydraulic shockwaves (Heart Regeneration Technologies GmbH, Innsbruck, Austria). Prior to use, the applicator is inserted into a sterile cover containing ultrasound gel. In order to ensure acoustic coupling between the applicator and the myocardium, continuous saline rinsing is applied throughout the procedure.

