#### No intervention (sham control) arm

In the sham control arm, the same manipulations are performed with an inactive shockwave applicator in direct contact with the ischaemic myocardium of the left ventricle as in the intervention arm. The sham treatment is performed during CABG surgery after bypasses are fully established while still on cardiopulmonary bypass.

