### Concealment mechanism {16b}

The randomization process will be realized independently from the clinical investigators using opaque envelops (fully blind randomization) For each participant enrolled on the study, one envelope will be opened at the end of the CABG procedure after opening the aortic clamp (bypasses fully established) while the patient is still connected to the heart-lung machine to get group allocation information.

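### Adverse events are counted from the start of CABG but the arm is assigned only at its end, so pre-allocation events dilute the exploratory all-adverse-event comparison and, at clamp opening, the ventricular-arrhythmia endpoint

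*Protocol article*

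**What the plan says.** **Counting window.** Under Adverse event reporting and harms {22}, an adverse event is one "occurring during or after the treatment (DESWT + CABG"). The baseline rule in the same section uses the same anchor: "Medical conditions/ diseases present before the treatment will only be considered adverse events if they worsen after the treatment".

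**Time of allocation.** Under Concealment mechanism {16b}, "one envelope will be opened at the end of the CABG procedure after opening the aortic clamp (bypasses fully established"), with the patient still on the heart-lung machine.

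**Time of the assigned procedure.** Experimental (intervention) arm: "The intervention is performed during CABG surgery after bypasses are fully established while still on cardiopulmonary bypass". The sham control arm has the same timing: "The sham treatment is performed during CABG surgery after bypasses are fully established while still on cardiopulmonary bypass".

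**Use of the count.** Safety and secondary analyses: "Occurrence of adverse events (safety) will be compared between treatment groups using chi-square tests" or Fisher's exact test. That sentence is not limited to device-related or post-allocation events. The same section says: "Appropriate statistical tests will be applied in an explorative manner only".

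**Safety endpoints.** Outcomes {12} gives the primary safety endpoint as "Occurrence of device-related complications (adverse device effects or serious adverse device effects) within 360 days". Of the three secondary safety endpoints, those on myocardial damage and infection are worded as device-related. Ventricular arrhythmia during the hospital stay is not. All three sit under a 6-day time frame whose starting point is not given.

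**The concern.** Everything from the start of surgery to the opening of the envelope happens before the patient belongs to an arm. Neither shockwave nor sham can have caused it, yet by definition it is an adverse event and is attributed to the arm drawn later. If occurrence is scored per patient, someone with an event before allocation is already positive, and a later event caused by the device leaves the score unchanged. An arrhythmia at clamp opening, before the applicator touches the heart, has the same effect on the ventricular-arrhythmia endpoint.

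At stake is the sensitivity of the one safety comparison that does not depend on anyone judging device-relatedness. That check has some value here, because Who will be blinded {17a} says that the principal investigator and the surgical personnel know the arm.

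There is also a wording fault. Sham patients never receive DESWT, so a definition that must serve both arms literally describes only one of them.

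**Working it through.** **1. Order of events in the text**

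| Step in the operation | Arm known? | Inside the adverse-event window? |
|---|---|---|
| Start of CABG to completed grafts and open clamp | No | Yes |
| Envelope opened | Becomes known | Yes |
| Shockwave or sham applied | Yes | Yes |
| Rest of the operation and follow-up | Yes | Yes |

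The baseline rule does not remove the first row. It sets aside only conditions present before the treatment, and the treatment is defined to include CABG.

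**2. Patients per arm**

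The only sizing in the article is for LVEF (Sample size {14}, conservative method). Effect size: (10.4 − 4.5)/8.7 = 5.9/8.7 = 0.678. A two-sided two-sample t test at 0.05 needs 36 per arm (power 0.81; 35 per arm gives 0.799). That is 72 analysed, and 72/0.9 = 80 enrolled, so the stated figures reproduce. They are used here only to fix 40 patients per arm. The article states no safety sizing or event rate to check.

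**3. Dilution**

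Let q be the probability of a pre-allocation event, equal in both arms and independent of later events. Let p_S and p_D be the post-allocation risks under sham and shockwave.

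- Observed risk in an arm: 1 − (1 − q)(1 − p).
- Observed difference: (1 − q)(p_D − p_S).

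For q = 10%, p_S = 20% and p_D = 50%, the observed risks are 1 − 0.9 × 0.8 = 28% and 1 − 0.9 × 0.5 = 55%. The difference is 27 points instead of 30, and the risk ratio 1.96 instead of 2.50.

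**4. Power** (Fisher's exact test, enumerated exactly, 40 per arm, two-sided 0.05). All rates are assumptions.

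| q | 20% vs 50%: difference | Power | 5% vs 25%: difference | Power | 10% vs 20%: difference | Power |
|---|---|---|---|---|---|---|
| 0 | 30.0 points | 0.75 | 20.0 points | 0.65 | 10.0 points | 0.16 |
| 5% | 28.5 | 0.69 | 19.0 | 0.50 | 9.5 | 0.13 |
| 10% | 27.0 | 0.63 | 18.0 | 0.39 | 9.0 | 0.11 |
| 20% | 24.0 | 0.51 | 16.0 | 0.25 | 8.0 | 0.08 |
| 30% | 21.0 | 0.40 | 14.0 | 0.19 | 7.0 | 0.07 |

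The loss is proportionally larger when the sham risk is low. For a modest excess such as 10% vs 20%, power is poor even at q = 0.

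**The case against.** A reader might infer that the trial's main safety conclusion, or any device signal, is diluted. The documents do not support that. The primary safety endpoint in Outcomes {12} counts device-related complications only. An event before applicator contact cannot properly be judged device-related, so correct attribution already removes it. The same applies to the two secondary safety endpoints worded as device-related. This part of the objection stands and limits the point to the all-adverse-event comparison and ventricular arrhythmia.

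The all-adverse-event comparison is explicitly exploratory, with no formal hypothesis testing. This also stands: the power figures show lost sensitivity, not a failed confirmatory test.

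Masking across event types needs a single any-event indicator, which the article does not specify. If events are tabulated by type, bleeding at cannulation cannot hide a later ventricular tachycardia, and q becomes the pre-allocation rate of that one type, probably smaller. This stands, although dilution within a type remains.

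A reader might also infer that arrhythmia before surgery counts towards the arrhythmia endpoint, because it refers to the hospital stay. The 6-day frame has no stated start, so that is conjecture. Arrhythmia at clamp opening is the firmer case.

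Finally, no document supports any particular q or a true excess of 20 to 30 points, and the present rule spares anyone who knows the arm from classifying onset. The first remark means that the size is illustrative only. The second is a real cost of the fix. Neither removes the mismatch, which is in the stated text and is not a detail left to an analysis plan.

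**Conclusion.** The point holds in limited form. The adverse-event window opens before allocation, so the exploratory all-adverse-event comparison and, at clamp opening, the ventricular-arrhythmia endpoint take in events that the assigned procedure could not have caused. Because these are balanced in expectation, the result is attenuation and added noise, not a systematic advantage for one arm.

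The per-patient risk difference shrinks by the factor (1 − q). With assumed risks of 20% and 50% and 40 per arm, Fisher power falls by about 6 points at q = 5% (74.9% to 68.5%) and 12 points at q = 10% (74.9% to 62.5%). This rests on assumed event rates, on independence of earlier and later events, and on per-patient scoring. The primary safety endpoint in Outcomes {12} is untouched if attribution is done correctly. The failure of the definition to describe the sham arm depends on no assumption. Severity: CONSIDER.

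**What to change.** - Keep recording and reporting all adverse events from the start of surgery.
- In Adverse event reporting and harms {22}, replace the parenthesis with wording that covers both arms: CABG with shockwave or sham application.
- For the between-arm adverse-event comparison and the ventricular-arrhythmia endpoint, count events with onset or worsening after one fixed time point, the opening of the envelope, in both arms.
- List earlier intra-operative events separately, and show the all-event count as a sensitivity tabulation.

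**Cost.** A few sentences of text, plus classification of intra-operative onset from the timed operative record. Because surgical staff know the arm, this should be done without reference to arm where possible. Trial status gives recruitment as closed on 01.06.2022, so the work depends on what those records captured. Events whose onset cannot be timed should count as post-allocation in both arms, which leaves some of the dilution in place but keeps the rule symmetric.
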